#### Random Assignment

After completing the baseline assessment, participants were assigned to a condition through an urn randomization procedure. The urn randomization procedure provided balance across age (18-24 and 25-34 years), race/ethnicity (Latino/Hispanic and all other race/ethnicities), and HIV care continuum status (linked, nonlinked to HIV care). Participants were randomized into 1 of the 2 conditions: Group A—immediate text message intervention delivery (n=61) or Group B—delayed text message intervention delivery (n=69) whereby participants were delivered the text-messaging intervention after a 90-day delay period. Both groups received the same 90-day text-messaging intervention. The randomized 2-group repeated measures design assessed participants at 3, 6, 12, and 18 months post randomization.

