### Statistical Analyses

Table 2 provides all evaluation outcomes and their chosen measurement models. Power calculations are based on assumptions of alpha=.05 (2-tailed tests), a sample size of 130 HIV-positive young transgender women, and a power standard of 0.80. It was calculated that logistic regression analyses of primary outcomes would be able to find a minimum detectable odds ratio of 2.98 for linkage/uptake of ART and achievement of an undetectable viral load (the primary outcomes of interest).

**Table 2 table2:** Study outcomes and measurement models.

Primary outcome	Measurement model
Linkage to HIV primary care (self-report and EMR^a^/EHR^b^ abstraction)	0= Participant did not attend HIV medical visit within 3 months of enrollment; 1= Participant attended within the first 3 months
Prescribed ART^c^ medication (self-report and EMR/EHR abstraction)	0=Participant is not prescribed HIV medication; 1=Participant is prescribed HIV medication
Retention in HIV primary care (self-report and EMR/EHR abstraction)	0=Participant did not attend a second HIV care appointment after the initial 3 months; 1=Participant attended an additional HIV primary care visit after the initial 3 months
ART adherence (self-report)	Ordinal scale (Likert)
Viral load monitoring (self-report and EMR/EHR abstraction)	Binary (0=>200 copies/mL, 1=<200 copies/mL)

^a^EMR: electronic medical report.

^b^EHR: electronic health report.

^c^ART: antiretroviral therapy.

All regression analyses assess assumptions of normality and model fit. In addition to the primary outcomes listed in Table 2, participants were assessed for changes in their HIV-related self-efficacy from baseline to follow-up evaluations. The HIV-ASES scale was used to assess HIV self-efficacy, producing continuous values suitable for ordinary least squares (OLS) regression. In addition, if during implementation, a sufficient number of participants opted in to receive one or more of the postintervention retention/engagement text messages available through final distal follow-up evaluation, additional analyses were carried out to estimate the observed effect(s) of receiving these postintervention text messages.

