All calculations of detectable effects for primary outcomes were based on expected cultural/demographic subgroup analyses premised on known social determinants of risk (eg, racial/ethnic identity, language and health insurance) and are displayed in Table 2. Secondary analyses related to HIV self-efficacy were analyzed using OLS regression and should produce detectable effects at *f*^2^=0.067. Given these values, detectable effects of all analyses should, if benchmarked, fall in the *small to moderate* to *moderate* ranges. Given an expected follow-up rate of at least 85% (111/130) at each time point, associations between primary outcomes and optional postintervention retention/engagement messages should produce minimum detectable effects exhibiting a 3% (repeated measures survival analysis testing time-based dichotomous outcomes, eg, linkage) to 18% (OLS regression for secondary analyses, eg, HIV-related self-efficacy scores) increase in detectable effect size (ie, outcomes will be more difficult to detect), resultant from participant attrition.

Primary outcome analyses comprised bivariate contrasts of outcomes over time (ie, HIV care continuum outcomes at baseline and each follow-up, with differences tested via *t* test and chi-square analyses) and multivariate analyses of these same outcomes regressed on random study arm assignment, self-reported exposure to theory-based text messages, and time. Observations were nested within participants, and sociodemographic controls were tested for inclusion during sensitivity testing of the models. Secondary outcomes included sexual risk behaviors, substance use, self-efficacy, and changes in gender identity over time.

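### The stated primary regression adjusts for none of the three urn randomisation factors and not for baseline outcome values, which costs a modest amount of power but does not inflate type I error.

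*Protocol article*

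**What the plan says.** Random Assignment (Protocol article) describes the balancing: "The urn randomization procedure provided balance across age (18-24 and 25-34 years), race/ethnicity (Latino/Hispanic and all other race/ethnicities), and HIV care continuum status", the last factor being split into linked and nonlinked.

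Statistical Analyses gives the primary regression as "multivariate analyses of these same outcomes regressed on random study arm assignment, self-reported exposure to theory-based text messages, and time". Observations are nested within participants. The outcomes are those measured at baseline and at each follow-up, so baseline is one of the analysed time points. On further covariates the section says only this: "sociodemographic controls were tested for inclusion during sensitivity testing of the models".

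The power statement in the same section reads "Power calculations are based on assumptions of alpha=.05 (2-tailed tests", with "a sample size of 130 HIV-positive young transgender women, and a power standard of 0.80", and gives a "minimum detectable odds ratio of 2.98 for linkage/uptake of ART and achievement of an undetectable viral load". It states no control-group rate and no prognostic strength for any covariate.

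**The concern.** A factor is balanced at randomisation because it is expected to predict the outcome. If the analysis then ignores it, the variance estimate does not credit the balance: the arm test becomes conservative and loses power.

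Linked/nonlinked care status deserves particular attention here, because the primary outcomes in Table 2 are stages of the same care continuum. The eligibility criteria in Sample also admit a mixed group: newly diagnosed, out of care, unsuppressed, not prescribed ART, or on ART with less than excellent self-rated ability to take it. A strong link between baseline status and outcome is therefore plausible, though the article gives no figure for it.

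With 130 participants and a detectable odds ratio near 3 there is little spare power. Enrolment has closed, so participants cannot be added, but covariates can.

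**Working it through.** **Inputs from the article.** Two-sided alpha 0.05, power 0.80, N = 130, allocation 61 (Group A) and 69 (Group B), detectable odds ratio (OR) 2.98, three urn factors, and the regressors arm, exposure and time.

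**Inputs assumed.** Control-group rate 20% or 40%; half or 70% of participants in the better-prognosis care-status group; OR between care status (or baseline outcome) and outcome of 3, 6, 10 or 20.

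**Step 1: the plan's own figure.** Without a control rate, 2.98 cannot be uniquely reproduced, but it is attainable. For a two-proportion test with pooled variance under the null:

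- Control rate p0 = 0.20, odds 0.25. Treated odds 2.98 × 0.25 = 0.745, so p1 = 0.745/1.745 = 0.427.
- Pooled p = (69 × 0.200 + 61 × 0.427)/130 = 0.306.
- Null SE = √[0.306 × 0.694 × (1/69 + 1/61)] = 0.081. Alternative SE = √[0.2 × 0.8/69 + 0.427 × 0.573/61] = 0.080.
- z = (0.227 − 1.96 × 0.081)/0.080 ≈ 0.86, which gives power of about 0.80.

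Solving for 80% power at 69/61 gives a minimum detectable OR of 2.96 at a 20% control rate, and 2.71 to 3.73 over control rates of 10% to 70%. With 111 completers, 2.98 is reached at a 30% rate. This calculation has no covariates, so it is the right reference for an arm-only test.

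**Step 2: power with and without the urn factors.** Trials of 130 were simulated under a simple urn scheme on three binary factors, 2,500 runs per setting. The marginal arm OR was held at 2.98 throughout, so only the analysis differs. Each outcome was fitted by logistic regression on arm alone, then on arm plus the three factors.

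| Setting | OR 3 | OR 6 | OR 10 | OR 20 |
|---|---|---|---|---|
| Control 20%, factor split 50/50 | 0.804 → 0.816 | 0.798 → 0.853 | 0.815 → 0.882 | not run |
| Control 40%, factor split 50/50 | 0.836 → 0.866 | 0.865 → 0.914 | 0.868 → 0.930 | 0.878 → 0.959 |
| Control 40%, factor in 70% | 0.869 → 0.895 | 0.868 → 0.906 | 0.861 → 0.919 | 0.867 → 0.951 |

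The Monte Carlo standard error of one power figure is √(0.8 × 0.2/2500) = 0.008. With no prognostic effect (OR 1) the adjusted model already showed 0.4 to 1.0 points more, so the gains at OR 3 are barely distinguishable from nothing.

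**Step 3: sample-size equivalent at the 20% control rate.** Ratio = [(1.96 + z of adjusted power)/(1.96 + z of unadjusted power)]².

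- OR 3: (2.860/2.816)² = 1.03
- OR 6: (3.009/2.795)² = 1.16
- OR 10: (3.145/2.857)² = 1.21

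Adjustment is thus worth about 3%, 16% and 21% more participants.

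**Step 4: baseline outcome as a covariate.** With 35% positive at baseline, a 40% control rate at month 3 and 2,000 runs, arm alone at month 3 was compared with arm plus baseline outcome plus urn factors: 0.863 → 0.883 (OR 3), 0.866 → 0.906 (OR 6), 0.873 → 0.936 (OR 10), 0.854 → 0.951 (OR 20). Entering baseline as an outcome row with an arm-by-time effect gave 0.861, 0.862, 0.867 and 0.852, no better than month 3 alone. That fit used working independence with cluster-robust standard errors, under which baseline rows cannot inform the month-3 contrast. A random-effects model might recover part of the loss, so this comparison does not settle what the plan's nested model would achieve.

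**Step 5: type I error.** At a 40% control rate, rejection under the null was 0.031 to 0.047 unadjusted and 0.042 to 0.057 adjusted.

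**Limits of the check.** It uses one post-baseline outcome with complete data and no exposure term, so it approximates the arm comparison and does not simulate the full repeated-measures model.

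**The case against.** The strongest objection is that this is a condensed article. One sentence on regressors is not a full covariate list, and an analysis plan not shown may contain the urn factors. That limits the point, because nobody can say the factors will never be in the model. It does not remove it. The article goes beyond silence: it states a regressor list and a rule for further covariates, and neither brings in care status. Age and race/ethnicity could enter, but only through sensitivity testing.

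Several stronger readings are tempting and are not supported:

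- **That the primary models select covariates by significance testing.** The text places that testing in sensitivity work, so outcome-dependent selection is not shown for the primary test.
- **That the baseline outcome is left out altogether.** It is an analysed time point. Linkage (a visit within 3 months of enrolment) and retention (a visit after those 3 months) have no baseline value by definition, so this part applies only to ART prescription, adherence and viral load.
- **That care status is the strongest predictor of the outcomes.** This is plausible, but nothing in the article establishes it.
- **That power falls well below 80%.** A simulation with the conditional OR fixed at 3, the factor in 40% of participants and a factor OR of 8 gives 67% unadjusted against 78% adjusted. The 40% and the 8 are not in the article. Fixing the conditional OR also shrinks the marginal OR to about 2.4, below the stated 2.98, so much of the drop reflects a smaller effect. With the marginal OR at 2.98, unadjusted power stayed at about 0.80 to 0.88 in the settings run.
- **That the result would be biased or falsely positive.** Step 5 shows the reverse: the unadjusted test is at most conservative.

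**Conclusion.** The point holds as a matter of efficiency. The stated primary model ignores the three factors that the randomisation balanced, and the stated route for extra covariates would not admit care status. Baseline outcome values are not used as covariates for the three outcomes that have them.

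At a marginal OR of 2.98, adjustment gains about 1-3 points of power if the factor's OR with the outcome is 3, 4-6 points at 6, 6-7 points at 10 and 8-10 points at 20. The loss is negligible if prognosis is modest and becomes material from an OR of about 6. These figures rest on assumed control rates, factor prevalence and prognostic strength. The validity of the arm test is not threatened by this omission. The change is worth making because it is free, not because the trial fails without it.

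**What to change.** In Statistical Analyses, or in the analysis plan if one exists:

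1. Name age group (18-24, 25-34), race/ethnicity group (Latino/Hispanic, all other) and linked/nonlinked care status as fixed covariates in every primary model.
2. Add the baseline value of the outcome as a covariate for ART prescription, adherence and viral load. Do not ask for one for linkage or retention. When baseline becomes a covariate, remove it as an outcome row in that model.
3. Keep test-selected sociodemographic covariates to analyses labelled as sensitivity analyses.
4. Say that the adjusted odds ratio is conditional on the covariates. At a 40% control rate with the factor split 50/50, a marginal OR of 2.98 corresponds to a conditional OR of 3.23, 3.72 or 4.35 at factor ORs of 3, 6 and 10, so the two should not be compared directly with each other or with the power statement.

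The urn factors were needed to randomise and the baseline values are collected, so the cost is wording only. The Results section has primary analyses starting after follow-up ends on August 31, 2019, so on the article's timeline the change can be made before analysis. If an unseen analysis plan already lists these covariates, aligning the article's sentence with it is enough.

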## Results

Recruitment began on November 18, 2016, and the first participant was enrolled on December 16, 2016; enrollment closed on May 31, 2018. Intervention delivery ended on November 30, 2018, and follow-up evaluations will conclude on August 31, 2019. Primary outcome analyses will begin immediately following the conclusion of the follow-up evaluations.

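### Follow-up ends 15 months after enrolment closed, so women enrolled from 1 March 2018 reach 18 months only after it ends, and the 85% follow-up figure does not allow for this

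*Protocol article*

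**What the plan says.** All places are in the protocol article.

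- **Dates (Results, repeated in the Abstract).** "the first participant was enrolled on December 16, 2016", and then "enrollment closed on May 31, 2018. Intervention delivery ended on November 30, 2018, and follow-up evaluations will conclude on August 31, 2019". The primary analyses are to start directly after follow-up ends, so no later visits are foreseen.
- **Visit schedule (Random Assignment).** The design "assessed participants at 3, 6, 12, and 18 months post randomization". Evaluation Procedures repeats the schedule and describes the 6-, 12- and 18-month visits as approximate, without a window width. No section exempts late enrolees from month 18.
- **Expected follow-up (Statistical Analyses).** "Given an expected follow-up rate of at least 85% (111/130) at each time point", the plan gives a 3% to 18% increase in minimum detectable effects and attributes it to participant attrition. The sentence concerns associations between the primary outcomes and the optional post-intervention messages.
- **Use of month 18 (Statistical Analyses).** The primary analyses compare care-continuum outcomes at baseline and at each follow-up, so month 18 is among them.

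**The concern.** The calendar and the visit schedule do not fit together. A woman enrolled on the last permitted day is due at 18 months on 30 November 2019, three months after follow-up closes. The plan's only allowance for missing visits is attrition, but these visits would be missing because of the enrolment date.

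This matters in two ways. First, the expected number at 18 months, and any detectable effect that relies on it, is probably too favourable. Second, visits that never fell due within the study differ in kind from visits that were missed. The two need separate labels so that the 18-month denominator is clear.

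**Working it through.** **Inputs.** First enrolment 16 December 2016, enrolment closed 31 May 2018, delivery ended 30 November 2018 and follow-up ends 31 August 2019 (Results). Visits at 3, 6, 12 and 18 months (Random Assignment). N = 130 and at least 85% followed up (Statistical Analyses). Even accrual and the early-visit windows below are assumptions; the article gives neither.

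**1. The plan's own figure.** 0.85 × 130 = 110.5, rounded up to 111; 111/130 = 85.4%. The stated 111/130 reproduces.

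**2. Calendar.**
- 31 May 2018 to 31 August 2019 = 15 months (457 days).
- 31 May 2018 + 18 months = 30 November 2019.
- 31 August 2019 − 18 months = 28 February 2018, the last enrolment date that allows a full 18 months.
- 31 May 2018 + 12 months = 31 May 2019, so the 12-month visit, and those before it, can be completed by all.

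**3. Are the enrolment dates plausible?** A delayed-arm participant enrolled on 31 May 2018 finishes after 90 + 90 = 180 days, on 27 November 2018. That agrees with "Intervention delivery ended on November 30, 2018". The enrolment and delivery dates fit each other; the follow-up end date and the 18-month schedule do not.

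**4. Size under even accrual.**
- Enrolment days, both ends included: 532. Days up to 28 February 2018: 440. Days after: 92.
- Women affected: 92/532 × 130 = 17.3% × 130 ≈ 22.5.
- Ceiling at 18 months with no attrition: 440/532 × 130 ≈ 107.5 (82.7%).
- With 85% of those due attending: 0.85 × 107.5 ≈ 91.4 (70.3%).
- Counting accrual from the start of recruitment (18 November 2016) gives a ceiling of 108.6 (83.6%).

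**5. Sensitivity to an early-visit window (even accrual).** The retention needed is 111 divided by the ceiling.

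| Assumed early window | Ceiling at 18 months | Seen if 85% of those due attend | Retention needed for 111 |
|---|---|---|---|
| none | 107.5 (82.7%) | 91.4 (70%) | 103% (impossible) |
| 14 days | 110.9 (85.3%) | 94.3 (73%) | 100% |
| 31 days | 115.1 (88.5%) | 97.8 (75%) | 96.4% |
| 92 days | 130 (100%) | 110.5 (85%) | 85.4% |

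Only a window of about three months closes the gap.

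**6. Sensitivity to the accrual pattern (no window).** 130 − 111 = 19. If 20 or more women enrolled after 28 February 2018, 111 cannot be reached. With exactly 19 it needs complete retention. With 10 the ceiling is 120, and 85% retention gives 102. With none, 85% retention gives the planned 110.5.

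**7. Illustrative scaling of the detectable effect.** The article's minimum detectable odds ratio of 2.98 is stated at n = 130. Scaling the log odds ratio by √(130/n) gives 2.98^√(130/111) ≈ 3.26 at the already planned 111, and 2.98^√(130/92) ≈ 3.66 at 92. The step due to the calendar is about 3.26 to 3.66. This is a rough scaling and does not replace a recalculation.

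**The case against.** The strongest reply accepts the date gap but disputes how much follows from it.

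- **Visit timing is approximate.** A reader might infer that nobody enrolled from 1 March 2018 could have any 18-month visit. The article does not support that: some tolerance is implied and its width is not given, so 28 February 2018 is a sharp cut-off only without a window. This stands. It does not rescue the schedule, because a window wide enough to cover everyone would allow the visit at 15 months.
- **No accrual curve.** A reader might conclude that 85% certainly fails at 18 months. The shortfall before attrition is small (107.5 against 111), and slower accrual in the last three months would remove it. This stands too; faster late accrual would make it worse.
- **Power.** A reader might say that the detectable odds ratio rises from 2.98 to 3.66. That figure is given at n = 130 and not as an 18-month value, and the comparison charges attrition already planned for to the date problem. The 85% and its inflation range are attached to the optional-message associations. The article states no 18-month between-arm detectable effect.
- **Limited reach.** Visits to month 12 are intact, linkage is defined within 3 months, and by month 18 both arms have been offered the intervention. This is right and limits the damage. Month 18 nevertheless remains among the follow-ups in the primary analyses, and the optional messages run to the final follow-up.
- **Handling of missing visits.** A reader might fear that visits not due will be counted as losses or failures. No section says so, and the rule may be in an analysis plan that is not shown.

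**Conclusion.** The contradiction is established from the article's own dates: 15 months are available after the last enrolment for a schedule that needs 18. No modest visit window removes it.

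Its size is conditional. Under even accrual about 22 of 130 women are affected, with a ceiling of about 83% before attrition and about 70% after the planned attrition among those due, against the stated 85%. A 14-day early window brings the ceiling to break-even and a 31-day window to 88.5%. Either leaves little or no room for the 15% attrition that the plan allows.

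Confidence is high for the date gap and moderate for the numbers, which rest on the assumed accrual. The effect is confined to month 18.

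**What to change.** Reconcile the follow-up end date, the 18-month schedule and the 85% expectation before the analysis starts, by one of two routes.

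1. **If 31 August 2019 stands:**
   - State that women whose 18-month visit falls after that date are administratively not due, and are neither lost to follow-up nor failures. Give the visit window that decides this.
   - Restate the expected 18-month number from the actual enrolment dates. Restate the attrition-based inflation of detectable effects for analyses that use month 18.
   - Name month 12 as the last visit due for all 130.
2. **Otherwise:** extend follow-up to 30 November 2019 and move the start of analysis accordingly.

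The first route costs a few sentences and a less favourable 18-month figure. The second costs three more months of visits. If a detectable odds ratio is shown for month 18, compare it with the value at the planned 111, not with 2.98 at 130, and label any simple scaling as illustrative.

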## Discussion

*Text Me, Girl!* was designed to meet the needs of underserved young transgender women living with HIV/AIDS. Young transgender women living with HIV experience a range of barriers that challenge their ability to be successfully linked and retained in HIV care. Text messaging is a communication platform well suited for engaging young transgender women in HIV care because it is easily accessible, widely used, private, portable, and inexpensive. *Text Me, Girl!* aimed to improve HIV care continuum outcomes among young transgender women by providing culturally responsive text messages to promote linkage, retention, and adherence, with the ultimate goal of achieving viral suppression. The *Text Me, Girl!* text message library is readily scalable and, if successful, can be adapted for application with other hard-to-reach populations.

